### Statistical analysis

The modified intention-to-treat principle will be used such that all subjects who attend the first intervention session will be analyzed [50]. The success of randomization will be tested by comparing baseline characteristics of the study groups with potentially confounding variables included as covariables. Analysis of variance will be used to compare continuous variables. Categorical variables will be compared via chi-square test. The effect of treatment on time-related outcome measures such as lapse and relapse will be analyzed by life-table survival analysis. Binary linear generalized estimating equations (GEE), with autoregressive correlation matrices, will be employed to determine differences between integrated care and usual care groups on change in anxiety or mood symptoms. A series of regression analyses will be performed to assess the role of symptomatic change in alcohol consumption and vice versa. Last-point carried forward or multiple imputation will be used to determine the scores of participants who drop out or are lost to follow-up. One previous study [9] with a similar design (N = 35) demonstrated that combined CBT treatment of alcohol dependence and comorbid depression significantly improved alcohol use outcomes with a moderate effect size. Power analysis has thus been performed such that a sample of 60 subjects (30 per group) has 80% power of detecting a moderate difference between the two arms of care on alcohol use outcomes at alpha = 0.05.

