### Randomization and allocation concealment

Randomization will be stratified according to concomitant selective serotonin reuptake inhibitor (SSRI) use and will by referring to the consecutively assigned subject identification number to a matched numbered envelope containing a random assignment card. Assessors will be blind to treatment allocation for the follow-up diagnostic interviews, and the same assessor will not assess the participant they assessed at baseline. Participants were asked not to mention their therapist or details of their therapy during their follow-up assessment. In order to evaluate the blinding process, assessors will be asked to which treatment group they believe each participant was allocated. A paper wall will be implemented whereby the researchers that obtain follow-up data will have no knowledge of treatment-group allocation.

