### Intervention

#### Usual care

Counseling for the treatment of alcohol dependence will continue in accordance with standard practice at the participating treatment site [40]. This entails brief individualized motivation enhancement therapy (ie, feedback of assessment findings, reinforcement, empathy, enhancing client’s own motivation). Participation in treatment sessions will be recorded. As quality-control measures, counselors will be supervised by senior staff and engage in weekly meetings, and treatment will be delivered according to the evidence-based treatment manual of Jarvis et al. [40].

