#### Intervention for alcohol and comorbid anxiety and/or mood disorder

Structured interviews will be audiotaped and reviewed by the clinical team to develop consensus case formulations. Trained therapists will deliver specific CBT interventions based on evidence-based treatment manuals for alcohol use, anxiety, and depressive disorders (Table 1). Cognitive restructuring and graded exposure or behavioral experiments are techniques that are common to CBT for most of these individual disorders. Cognitive restructuring involves helping patients identify the key beliefs they hold about themselves, the future, the outside world, and other people that maintain their drinking, anxiety, or depression and assisting them to dispute and develop more helpful alternative beliefs. Graded exposure and behavioral experiments involve the gradual and programmed confronting of feared situations and has been argued to be the single most successful technique for overcoming phobias. These are necessarily brief descriptions for therapy that are well-documented in the treatment manuals displayed in Table 1. These manuals will be adapted for use with an alcohol-dependent population, and cognitive-behavioral coping skills and motivational enhancement strategies for alcohol consumption will be used where appropriate [41,42]. We expect different and complex interactions between the comorbid disorders, because the patients targeted for this study will experience significant comorbidity. An individualized case formulation, which hypothesizes the factors that maintain each individual’s problems, will be constructed following assessment using standard methods [39] (Table 2). The interventions will be delivered in seven to 10 sessions. To ensure that therapists adopt and maintain the principles of the therapy as described in the manual, sessions with consenting subjects will be audiotaped for discussion with the therapist early in the study (n = 4 per therapist) and at random times later in the study (n = 4 per therapist).

**Table 1 T1:** Cognitive behavioral therapy manuals forming the basis of integrated care for depression, anxiety, and alcohol use disorders

**Diagnosis**	**Manual**
Depression	Persons et al. [43]
Social phobia	Rapee [44] Rapee & Sanderson [45]
Panic disorder or agoraphobia	Andrews et al. [46]
Generalized anxiety disorder	Andrews et al. [47]
Post-traumatic stress disorder	Foa & Rothbaum [48], Najavits [49]
Alcohol use disorders	Monti et al. [41] Miller et al. [42]

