**Table 2 T2:** Schedule of assessments

**Measure**	**Schedule**
Mini Social Phobia Inventory (Mini-SPIN)	Intake screening
Kessler Psychological Distress Scale (K10)	Intake screening
Comorbidity Suspicion Checklist (CSC)	Baseline (step 1*)
DSM-IV assessed dependence	Baseline (step 1)
Alcohol Dependence Scale (ADS)	Baseline (step 1), Weeks 12, 16, 24
Obsessive Compulsive Drinking Scale (OCDS)	Baseline (step 1), Weeks 12, 16, 24
Stages of Change Readiness and Treatment Eagerness (SOCRATES) Scale	Baseline (step 1), Weeks 12, 16, 24
Alcohol Abstinence Self-Efficacy (AASE)	Baseline (step 1), Week 12, 16, 24
Short-Form Health Survey (SF-12)	Baseline (step 1), Week 12, 16, 24
Depression Anxiety Stress Scale (DASS)	Baseline, Week 3 (step 2**), 12, 16, 24
Insomnia Severity Index (ISI)	Baseline, Week 3 (step 2), 12, 16, 24
Glasgow Sleep Effort Scale (GSES)	Baseline, Week 3 (step 2), 12, 16, 24
Timeline Follow-back (TLFB)	Baseline, Week 3 (step 2), 12, 16, 24
Anxiety Disorders Interview Schedule (ADIS)	Week 3 (step 2), Week 16
Hamilton Rating Scale for Depression (HRSD)	Week 3 (step 2), Week 16

*Step 1 = week 0 preceding three-week alcohol stabilization phase.

**Step 2 = formal diagnosis for depression and/or anxiety disorder preceding randomization to usual care or integrated care.

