### Outcome measures

Primary outcomes include time to consumption of any alcohol (lapse) as identified by self-reported alcohol consumption; time to relapse as ≥ 4 drinks for women, ≥ 6 drinks for men; amount of alcohol consumed (total abstinence and average consumption per drinking day). Secondary outcomes include improvement in depressive or anxiety symptoms (DASS) or alcohol dependence severity (ADS); biological markers of alcohol consumption at 6, 12, 16, and 24 weeks (carbohydrate-deficient transferrin, liver function, and mean corpuscular volume); episodes of alcohol-related harm (psychosocial, occupational, forensic, medical); and clinician-rated severity of anxiety and depression based on ADIS and HRSD.

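### The analysis set keeps only randomized patients who attend a first session, a post-randomization event that may bias the comparison in either direction

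*Protocol article*

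**What the plan says.** All references are to the protocol article.

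- **Analysis set (Statistical analysis).** "The modified intention-to-treat principle will be used such that all subjects who attend the first intervention session will be analyzed".
- **Timing of randomization (Table 2, footnote).** "Step 2 = formal diagnosis for depression and/or anxiety disorder preceding randomization to usual care or integrated care". The Procedure and Step 2 sections agree: patients are assessed, then randomized, then treated.
- **Blinding (Randomization and allocation concealment).** "Assessors will be blind to treatment allocation for the follow-up diagnostic interviews". Researchers who collect follow-up data are also kept unaware of allocation. No blinding of patients or therapists is described, and "Participants were asked not to mention their therapist or details of their therapy during their follow-up assessment".
- **The two arms.** For usual care, "Counseling for the treatment of alcohol dependence will continue in accordance with standard practice at the participating treatment site", and participation in sessions is recorded. For integrated care, "The interventions will be delivered in seven to 10 sessions".
- **Primary outcomes (Outcome measures).** These include "time to consumption of any alcohol (lapse) as identified by self-reported alcohol consumption", time to relapse and amount consumed.
- **Missing data (Statistical analysis).** "Last-point carried forward or multiple imputation will be used to determine the scores of participants who drop out or are lost to follow-up".
- **Sample size.** The Participants section expects 60 patients to be randomized. The power statement rests on 60 (30 per group), 80% power and alpha 0.05.

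The article states no analysis of all randomized patients, either as the primary or as a sensitivity analysis.

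**The concern.** Randomization makes the two groups comparable at the moment of allocation. Attendance at a first session comes later and is partly the patient's decision. Selecting on it can undo that comparability if the arms differ in how many patients stay away, or in which patients do. Blinding the assessors does not protect against this, because they do not decide who attends.

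The Background says that patients with this comorbidity drop out more often and relapse sooner, so some non-attendance linked to drinking is plausible.

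Three things are at stake:

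- the validity of the comparison on drinking outcomes;
- the question answered, because the aim is effectiveness against usual care in an outpatient service, where failure to take up the treatment is part of the result;
- the analyzed number, because the power statement makes no allowance for randomized patients who are then excluded.

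The imputation rule does not repair this. As written, it applies to drop-outs and losses to follow-up, and never-attenders have already left the set.

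**Working it through.** **Inputs from the article.** 30 per group, alpha 0.05 and 80% power. The article gives no rate of first-session non-attendance and no outcome gap between attenders and non-attenders. Every such figure below is an assumption.

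**1. The plan's own figure.** The article calls the target difference moderate and gives no number, so its 80% cannot be reproduced directly. The standardized difference that gives 80% two-sided power at 30 per group is

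d = (1.960 + 0.842) × √(2/30) = 2.802 × 0.258 = 0.723.

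This d serves below only as a reference point.

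**2. Bias with no true effect.** Let a fraction p of an arm never attend, and let those patients do δ SD worse than attenders. If the whole arm has mean 0, the attenders have mean −δp. The spurious difference between arms is therefore δ(p₁ − p₀). With SE = √(1/n₁ + 1/n₀) and n = 30(1 − p), the type I error is P(Z > 1.96 − bias/SE) + P(Z < −1.96 − bias/SE).

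| No-shows | δ | Bias (SD) | n analyzed (expected) | SE | Type I error |
|---|---|---|---|---|---|
| 20% v 20% | 1.0 | 0 | 24 v 24 | 0.289 | 5.0% |
| 20% v 5% | 0.5 | 0.5 × 0.15 = 0.075 | 24 v 28.5 | 0.277 | 5.8% |
| 20% v 5% | 1.0 | 1.0 × 0.15 = 0.15 | 24 v 28.5 | 0.277 | 8.4% |
| 30% v 10% | 1.0 | 1.0 × 0.20 = 0.20 | 21 v 27 | 0.291 | 10.6% |

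For the third row: 0.15/0.277 = 0.541, and P(Z > 1.419) + P(Z < −2.501) = 0.078 + 0.006 = 0.084. Simulated t-tests (20,000 per scenario) gave about 5.7%, 8% and 10% for the three unequal rows. The same simulations analyzed on all randomized patients gave about 5% each time.

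**3. A second selection model.** Suppose the tendency to stay away correlates 0.3 to 0.5 with a worse outcome. The shift per arm is r·φ(c)/(1 − q), where q is the non-attendance rate and c the corresponding normal cut-off. The bias is then 0.07–0.12 SD for 20% v 5%, and 0.09–0.15 SD for 30% v 10% (type I error 6.1%–8.1%). This is the same order of size.

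Equal rates alone are not enough, because the kind of patient must match too. As an extreme, take 10% in each arm with correlations of +0.5 and −0.5. The bias is 2 × 0.5 × 0.1755/0.90 = 0.20 SD. At 20% in each arm it is 2 × 0.5 × 0.280/0.80 = 0.35 SD.

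**4. A binary illustration (invented counts).** Abstinence of 12/30 v 9/30 is a 10-point difference as randomized. Dropping five non-abstinent never-attenders from the first arm gives 12/25 v 9/30, or 48% v 30%, an 18-point difference.

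**5. Analyzed number.** Power at d = 0.723 is Φ(0.723 × √(n/2) − 1.96).

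| Never attend (both arms) | n per group | Power | To randomize for 60 analyzed |
|---|---|---|---|
| 0% | 30 | 80% | 60 |
| 10% | 27 | 76% | 60/0.9 → 67 |
| 20% | 24 | 71% | 60/0.8 = 75 |
| 30% | 21 | 65% | 60/0.7 → 86 |

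**The case against.** The strongest case for the plan is that the rule is pre-specified, openly labelled as modified and supported by a citation. Beyond that, much of what a reader might infer is not documented.

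- **That the rule is asymmetric by design.** A reader might take the statement that usual counseling will continue to mean that control patients are already in sessions, while integrated care needs a fresh start. The wording can equally mean that the service goes on offering its usual counseling. The Procedure section names only optional pharmacotherapy during stabilization. Because participation in usual-care sessions is recorded, a first session can be identified in that arm too.
- **That the bias favours integrated care.** This needs more no-shows in that arm and worse drinking among them, and the article documents neither. Patients with anxiety or depression who are allocated to alcohol counseling alone might stay away instead, which would push the bias the other way.
- **That patients know their arm when they decide whether to attend.** The article does not say when allocation is disclosed. The request not to mention the therapist applies at follow-up, after therapy has begun. If the arm were revealed only at the first session, attendance could not depend on it. Nor is the trial simply unblinded: it is assessor-blind.
- **That the size is known.** All rates and gaps are assumed. The model uses a continuous outcome, whereas time to lapse and time to relapse are analyzed by life-table methods.

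These objections limit what can be claimed, and each stands to that extent. They do not remove the core point: the article fixes a set defined by a post-randomization event, describes nothing that would make attendance independent of allocation, and states no all-randomized analysis beside it. Pre-specifying the rule does not remove selection that arises after allocation.

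**Conclusion.** The point holds as a risk created by a stated rule. It is not a demonstrated bias. The comparison may be biased in either direction if first-session non-attendance differs between arms in rate or in type of patient, and the bias is near zero if non-attendance is rare or alike in both.

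In the main hypothetical scenarios (no true effect, 30 per arm, continuous outcome), bias runs from 0 to about 0.15–0.20 SD, with type I error of about 8–10% at the upper end. The upper end assumes no-shows of 20% v 5% or 30% v 10% who do 1 SD worse. Opposite selection in the two arms could exceed it, but that is an extreme case. These figures do not carry over directly to the survival outcomes.

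Two consequences do not depend on any direction of bias. The rule estimates an effect among starters, which is not the stated effectiveness aim. Any non-attendance among the 60 randomized also takes the analyzed number below that on which the 80% power rests.

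**What to change.** 1. Make the primary analysis all randomized patients in their assigned arm, regardless of attendance.
2. Seek drinking data from never-attenders at the scheduled follow-ups. The Follow-up schedule section already provides for at least two contacts per patient and three reminder attempts.
3. Report first-session non-attendance by arm.
4. Keep the attended-first-session set as a labelled sensitivity analysis.
5. For never-attenders without follow-up, specify multiple imputation, with a sensitivity analysis that counts them as relapsed. Do not use the last-point-carried-forward option for them. Their last drinking values come from the stabilization period, and Step 2 requires abstinence or a clinically significant reduction for randomization. Carrying those values forward could score never-attenders as successes and replace one bias with another.

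The cost is a change of wording in the analysis plan, continued follow-up attempts for a few patients, a somewhat diluted estimate and a few more missing outcomes to handle. Step 5 is a necessary part of the change: widening the set while leaving the carry-forward option open would not be enough.

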## Methods

### Procedure

The flow of participants is outlined in Figure 1. The first phase of the study is to establish a stabilization period from alcohol for three weeks before entering the randomization step of the study. During the stabilization period, participants will have the option of pharmacotherapy using naltrexone (50 mg, 1 tablet daily), acamprosate (333 mg, 2 tablets 3 times daily, reduced to 4 per day for women weighing < 65 kg), or a combination of the two as medically prescribed based on physician judgment and participant preference. After a three- to four-week stabilization period, patients will undergo complete formal assessment for anxiety and depression. Those with a diagnosis of anxiety or depressive disorder, regardless of drinking outcome, will be offered the next step of care. The remaining participants will be monitored for a further nine weeks while receiving alcohol pharmacotherapy and/or usual counseling care. Patients to undergo the next phase will also continue to receive further alcohol pharmacotherapy as medically prescribed but will be randomized to one of two treatment groups: 1) integrated intervention for comorbid alcohol, anxiety, and/or depression, or 2) usual counseling care. Follow-up appointments will then be scheduled at weeks 12, 16, and 24 as described below.

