### Step 1: inclusion and exclusion criteria for study enrollment

Inclusion criteria are as follows: alcohol dependence according to DSM-IV criteria, with alcohol as the subject’s drug of choice; age 18–65; adequate cognition and English-language skills to give valid consent and complete research interviews as assessed by the Mini Mental State Examination (MMSE); willingness to give written consent; abstinence from alcohol for between three and 21 days (standard clinical criteria for use of acamprosate or naltrexone); resolution of any clinically evident alcohol withdrawal as measured by the Clinical Institute Withdrawal Assessment for Alcohol–Revised (CIWA-Ar) [25]; and a positive score on the initial Comorbidity Suspicion Checklist (CSC). The CSC is a brief assessment to be administered at the first appointment. It is comprised of a one-page checklist to be filled in by one of the assessing clinicians to screen for current anxiety/depressive symptoms, previous diagnoses of comorbid conditions (anxiety disorder or depression), a previous history of treatment for comorbid conditions (anxiety disorder or depression), and a positive score on either the Mini Social Phobia Inventory (Mini-SPIN) for social anxiety [26] or the Kessler Psychological Distress Scale (K10) measure of psychological distress [27] for anxiety and depression.

Exclusion criteria include active major psychiatric disorder associated with significant suicide risk, pregnancy or lactation, advanced liver disease (hepatocellular failure, variceal bleeding, ascites, or encephalopathy), or other serious medical illness that would interfere with adherence to the study protocol.

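### The drinking analyses do not carry the SSRI stratifier, and covariables appear only in a sentence that tests whether randomization succeeded (minor)

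*Protocol article*

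**What the plan says.** All references are to the protocol article.

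- **Randomization and allocation concealment:** "Randomization will be stratified according to concomitant selective serotonin reuptake inhibitor (SSRI) use". No other stratifier is named.
- **Statistical analysis:** "The success of randomization will be tested by comparing baseline characteristics of the study groups with potentially confounding variables included as covariables". This is the only mention of covariables. The section then names analysis of variance for continuous variables and adds: "Categorical variables will be compared via chi-square test". Neither sentence is expressly linked to the choice of covariates.
- **Statistical analysis, on lapse and relapse:** "The effect of treatment on time-related outcome measures such as lapse and relapse will be analyzed by life-table survival analysis". No stratum or covariate is attached.
- **Procedure:** during stabilization patients may take naltrexone, acamprosate or "a combination of the two as medically prescribed based on physician judgment and participant preference". After step 2, "Patients to undergo the next phase will also continue to receive further alcohol pharmacotherapy as medically prescribed". This applies to both arms.
- **Outcome measures:** "Primary outcomes include time to consumption of any alcohol (lapse) as identified by self-reported alcohol consumption". Relapse and amount consumed are also primary.

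**The concern.** Two things are fixed badly.

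First, a test of whether randomization succeeded answers no useful question. If allocation was properly random, every baseline difference is due to chance. Tying covariables to that comparison also leaves the covariate set open until the baseline table has been seen, and an adjusted result can then be disputed.

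Second, a factor used to stratify should appear in the analysis. Stratification removes the factor's contribution from the real variability of the arm difference, but an unadjusted test still counts it in the residual variance. The test becomes slightly conservative. A look at baseline balance will not point to this factor, because stratification is meant to balance it.

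Alcohol pharmacotherapy at step 2 is a natural companion covariate. It is known before allocation and is given for the drinking that the primary outcomes measure. What is at stake is precision, and an analysis that is settled in advance.

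**Working it through.** **The plan's own figure.** Statistical analysis claims 80% power with 60 patients (30 per group) for a moderate difference at alpha 0.05. No number is given for moderate, so the figure cannot be reproduced. Two-sided, a difference of 0.5 SD would give 48% power, and about 0.74 SD is needed for 80%. The point here does not depend on this; 0.74 SD is used below only so that the comparison starts near the stated power.

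**Inputs.** From the document: 30 per arm, alpha 0.05. Assumed, because the document gives no figures: a continuous outcome with residual SD 1; 24 of 60 patients (40%) on SSRI, balanced between arms by stratification; 50% on alcohol pharmacotherapy, not stratified; each factor shifting the outcome by *e* SD; a two-sided test.

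**Variance due to each factor**, p(1 − p)e², with *e* = 0.5:
- SSRI: 0.4 × 0.6 × 0.25 = 0.06
- Drug: 0.5 × 0.5 × 0.25 = 0.0625

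**Ignoring both factors.**
- Variance that the test uses: 1 + 0.06 + 0.0625 = 1.1225.
- Variance that the arm difference really carries, with SSRI balanced: 1 + 0.0625 = 1.0625.
- Ratio of standard deviations: √(1.0625/1.1225) = 0.973.
- Type I error: 2 × [1 − Φ(1.96/0.973)] = 4.4%.
- Expected test statistic: 0.74 × √15/√1.1225 = 2.866/1.0595 = 2.705.
- Power: Φ((2.705 − 2.002)/0.973) = Φ(0.723), about 76.5%. Simulation gives 76.6%.

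**Adjusting for SSRI only.** 2.866/√1.0625 = 2.780, so power is Φ(2.780 − 2.002) = Φ(0.778), about 78%.

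**Adjusting for both.** Φ(2.866 − 2.003) is 80.6% before allowing for chance imbalance in drug use. Simulation, which includes that, gives 79.7% power and 5.1% type I error.

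**Weak factors, *e* = 0.2.**
- Variance used: 1 + 0.0096 + 0.01 = 1.0196. Real variance: 1.01. Ratio: 0.995.
- Type I error is 4.9% and power is Φ((2.838 − 2.002)/0.995), about 80%. Simulated power with both factors fixed is 79.6–79.7%. There is essentially no difference.

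**Near-universal drug uptake (90%), *e* = 0.5.** The drug variance falls to 0.9 × 0.1 × 0.25 = 0.0225. SSRI adjustment alone gives 2.866/√1.0225 = 2.834 and power Φ(2.834 − 2.002), about 79.7%. Both factors give at most 80.6%, so the drug factor adds under 1 point.

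**Time-to-event outcomes.** The arithmetic above is for a continuous outcome and does not carry over exactly to lapse and relapse. A simulated log-rank test (exponential times, 60 patients, 40% on SSRI, hazard ratio 0.36) stratified by SSRI and drug together, so four strata, gave 78% power against 80% unstratified when each factor had a log hazard ratio of 0.2. At 0.5 it gave no gain (77–79% against 78–79%). A repeat with fixed-time censoring also lost about 2 points with weak factors. The Cox covariate model was not simulated.

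**The case against.** The strongest case against is that this is a condensed article, and that a covariate list and the handling of the stratifier often sit in an analysis plan that is not shown. That stands for the list itself: the text does not exclude either factor, and not naming them is not in itself an error. It does not cover the stated test of randomization success, which a later plan would have to replace, not merely fill in.

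A reader might go further and infer that covariates will be chosen by a 0.05 chi-square screen, which would miss most chance gaps of 20 points in drug use. The document does not support this. It states no threshold and no selection rule, and the sentence can also mean that confounders are included whatever the comparison shows.

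The miss rates are also fragile. With the total on drug fixed at 80% of 60, such a screen misses 80% of gaps of 20 points or more. With 80% as the underlying uptake rate, such gaps arise in 7.5% of trials and 40% are missed. No such rate belongs in the conclusion.

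It is also fair that the harm is small and that adjusting for pharmacotherapy is a choice, not an obligation. Step 2 status is only a proxy for later exposure. Uptake may be near-universal, since the step 1 entry criterion of 3 to 21 days' abstinence is described as "standard clinical criteria for use of acamprosate or naltrexone".

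**Conclusion.** The point holds as a minor one. The plan tests the success of randomization, ties its only mention of covariables to that test, and does not carry its sole stratifier into the drinking analyses. A reader should not infer a biased treatment effect: there is none across randomizations, and the type I error of the unadjusted test errs on the safe side in the continuous case.

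The loss is about 3 points of power if both factors have 0.5 SD effects, and essentially nothing at 0.2 SD. These sizes rest on assumed effects, SSRI share, uptake and true difference, and on a continuous outcome; the gain for lapse and relapse has not been quantified. The case for a change rests as much on settling the analysis before the baseline table is seen as on the power.

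**What to change.** Replace the sentence on the success of randomization with the following:

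- Present baseline characteristics by arm descriptively, without tests.
- Adjust the drinking analyses for SSRI stratum whatever the observed balance, with step 2 alcohol pharmacotherapy (any versus none) as one further covariate.
- For lapse and relapse, use a Cox model with these covariates, or a log-rank test stratified by SSRI only. Avoid a four-stratum log-rank test, which can lose about 2 points of power with 60 patients.
- For amount consumed, enter both as covariates.
- Report prescribing after randomization by arm, descriptively, and do not adjust for it, because treatment may influence it.

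The cost is a sentence or two of text and one or two degrees of freedom. In the continuous-outcome simulations this cost at most 0.3 points of power when both factors were weak. The drug factor brings little if nearly everyone takes medication.
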